2.3 Intermittent preventive treatment in children (sIPT or IPTc)

The two studies conducted in Tanzania, where malaria transmission is intense and perennial have shown that IPT during infancy has the potential to become a major tool for malaria control in highly endemic parts of Africa. However, in many parts of Africa, especially those where transmission is seasonal, the main burden of malaria is in older children who would not be protected by an IPTi scheme which is limited to infants only. Except for impregnated bednets, there are no other efficacious tools available for preventing malaria in these children. Thus, we have explored the feasibility of using the IPT approach to prevent malaria in older children.

With support from the Gates Malaria Partnership, a study was undertaken in 2002 in children in Niakhar, a typical Soudano-Sahelian area of rural Senegal where malaria transmission is seasonal and intense. A single dose of SP plus one day of artesunate were given to 600 children in September, October and November, whilst 600 other children received a placebo. The incidence of clinical malaria was reduced by 86% in children who received the intervention.

Cross-sectional surveys were undertaken before and after the administration of sIPT. The prevalence of *Plasmodium falciparum* parasitaemia at the end of the malaria transmission season in children who had received the drug combination was 69% less than in the control children (11%% versus 35%). However, molecular studies showed that there had been a selection of parasites with *dhfr* mutations associated with pyrimethamine resistance in the children who had received SP plus artesunate but not in the control group. Although there was no overall increase in the number of resistant parasites in the children who had received sIPT, because the prevalence of infection was markedly reduced in these children, this finding is a matter of concern.

A single dose of artesunate has not been effective in preventing selection for parasites carrying genetic markers of SP resistance. Although the intervention reduces the absolute number of parasites with resistant genes to SP because of the lower carriage of parasites induced, there is significant selection for resistant genotypes in the IPT group. 95% of parasites in IPT recipients carried triple mutations in *pfdhfr* compared to 75% of parasites in the placebo recipients. (figure 1).

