# V. Hypothesis

Three doses of artesunate combined with SP or amodiaquine, and Lapdap used alone will be equally as effective at preventing malaria in young Senegalese children when used for sIPT as a regimen of SP combined with one dose of artesunate and less likely to select for resistant parasites

Two major endpoints will be considered in this study (i) the incidence of clinical malaria in children receiving one of these four interventions, (ii) the prevalence of parasites carrying genotypes associated with resistance following sIPT at the end of the transmission season.

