2.2. Exclusion criteria

Reasons for exclusion will include any of the following:

Any conditions causing an inability to take or retain oral medication.

Any chronic illnesses or severe conditions such as tuberculosis, epilepsy, obvious mental retardation or failure to thrive.

Severe congenital diseases such as heart malformations

Intake of an anti-malarial other than chloroquine within the previous two weeks

Known allergy to any of the antimalarial drugs used in the trial.

1. Study design

We will use an open label randomised trial comparing the following regimens:

- Artesunate one day plus SP

- Artesunate given for three days plus SP

- Artesunate plus Amodiaquine both given for three days

- Lapdap for three days

One of these combinations will be randomly allocated to all participants and given three times in early September, early October and early November 2004.

1. Sample size calculations

The trial is powered as an ‘equivalence’ or ‘negative’ trial, with the outcome being the cumulative incidence of malaria, ie the proportion of children having at least one episode of malaria during the course of the study. AS3+SP is the comparator and is expected to have cumulative incidence of 20%, and we aim to show that this is no more than 30% in the other three arms. To allow for three comparisons — AS3+SP compared with each of the other three arms — we set the significance level to 5/3% (≈0.0167%), one-sided. With 80% power, we need 336 children per arm (Jones, Jarvis et al. 1996). We expect no more than 20% to be lost to follow-up, which raises this to 420 per arm, or 1680 in total.

For the secondary drug resistance endpoint, this implies 336×0.2=67 cases on AS3+SP. To be conservative, we assume the same number on the other arms (if they turn out to be less effective than AS3+SP, this will only increase the power for this secondary endpoint). Among these cases, based on our previous study, we expect the prevalence of *dhfr* mutations at codons 108, 59 and 51 to be 90% in the AS1+SP arm. The 67 cases per arm then give us 77% power to detect a difference of 20% (ie 70% prevalence) in the other arms, with a significance level of 5% (two-sided, (Fleiss 1981)).

1. Enrolment procedure and follow-up

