At the time of the cross-sectional surveys filter paper blood samples will be collected and stored at 4 o C prior to analysis of molecular markers for resistance. For those children parasite-positive by microscopy, DNA will be extracted from the filter paper samples using standard techniques and amplified using PCR (Djimde, Doumbo et al. 2001). The reaction products will be probed for defined mutations in the dihydofolate reductase (*dhfr*), dihydroptypteroate (*dhps*) (Peterson, Di Santi et al. 1991) and *pfcrt* genes of *Plasmodium falciparum* using SSOP (Alloueche, Silveira et al. 2000). The prevalence of *dhfr* and *dhps* mutations associated with resistance to pyrimethamine will be compared between pre and post sIPT treatment samples in children who receive SP plus artesunate or Lapdap. Children who receive amodiaquine plus artesunate will act as controls. Similarly changes in the prevalence of *pfcrt* mutations before and after treatment will be measured in children who receive sIPT with amodiaquine plus artesunate whilst samples from children who receive SP or Lapdap will act as controls

1. Assessments of adverse events

Adverse events will be defined as any signs or symptoms, which first develop or increase in severity within seven days after intake. Any serious adverse events such as death or admission to hospital which occur within one week of drug administration will be thoroughly investigated and reported within 24 hours to the DSMB. To determine the prevalence of minor side effects following drug administration such as headache, fever, weakness, abdominal pain, anorexia, nausea, vomiting, diarrhoea, rash, itching or sleep disorder 100 randomly selected participants in each treatment group will be visited at home seven days after each round of drug administration and a side effects questionnaire completed. (*appendix 5*) Field staffs who complete these questionnaires will be unaware of the treatment group to which the child belongs.

1. Participants withdrawal

Parents will be at liberty to withdraw their children from the study at any time for any reason; this decision will not prejudice their children receiving malaria treatment.

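### The resistance analysis in section VI.8 uses a different contrast (pre/post, AS+AQ as control) from the AS1+SP comparison that the protocol hypothesises and powers

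*Protocol*

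**What the plan says.** Four parts of the protocol bear on the resistance comparison.

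- **Section V (Hypothesis).** The other three regimens are expected to be as effective "as a regimen of SP combined with one dose of artesunate and less likely to select for resistant parasites". The resistance endpoint is "the prevalence of parasites carrying genotypes associated with resistance following sIPT at the end of the transmission season".
- **Section 4 (Sample size calculations).** The number available is derived as "this implies 336×0.2=67 cases on AS3+SP", and the same number is assumed for the other arms. Prevalence of *dhfr* mutations at codons 108, 59 and 51 is taken as 90% on AS1+SP. Power is stated as 77% to detect 70% in the other arms, at 5% two-sided.
- **Section VI.8 (Assessment of resistances to antimalarials).** The prevalence of *dhfr* and *dhps* mutations "will be compared between pre and post sIPT treatment samples in children who receive SP plus artesunate or Lapdap". The next sentence reads "Children who receive amodiaquine plus artesunate will act as controls". For *pfcrt* the roles are swapped. Genotyping is restricted: "For those children parasite-positive by microscopy, DNA will be extracted from the filter paper samples".
- **Section 13.3 (Measurements of study end-points and statistical analysis).** AS1+SP is called the comparator, with a rise from about 50% to 90%. AS3+SP is assumed to rise from 50% to no more than 70%. Results are to be tabulated by regimen, and no test is named for resistance.

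**The concern.** The trial exists because SP with one dose of artesunate selected for *dhfr* mutants in 2002. Section IV.2.3 says that AS3+SP is included to learn whether further artesunate doses prevent that selection. The resistance analysis therefore has to set AS3+SP, and the other two regimens, against AS1+SP. Section VI.8 places both SP arms under one description and measures them against AS+AQ. An analyst who follows it literally could report that the SP arms moved more than AS+AQ and still have no answer on AS3+SP against AS1+SP.

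A second matter concerns the denominator. The children genotyped in December are those infected after treatment, a group that the regimens themselves shape. A regimen that clears sensitive parasites well can show a higher mutant share among the few remaining infections while fewer children carry mutants. The study outline says the trial will identify the most suitable combination with resistance selection taken into account, so the measure used could influence that choice.

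**Working it through.** **1. The contrasts side by side**

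| Place | Comparison | Reference | AS1+SP and AS3+SP separated? |
| --- | --- | --- | --- |
| Section V | end of season, between arms | AS1+SP | yes |
| Section 4 | 90% vs 70%, between arms | AS1+SP | yes |
| Section 13.3 | 50→90% beside 50→70% | AS1+SP | yes, but no test named |
| Section VI.8 | pre vs post | AS+AQ | no |

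**2. The plan's own figure**

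Inputs from section 4: p1 = 0.90, p2 = 0.70, n = 67 per arm, 5% two-sided, Fleiss method.

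- Continuity correction: n = (m/4)·[1 + √(1 + 4/(m·d))]² with d = 0.20. For n = 67, the effective m is 57.4.
- z = [d·√m − 1.96·√(2·0.8·0.2)] / √(0.9·0.1 + 0.7·0.3) = (1.515 − 1.109)/0.548 = 0.74.
- Power = 77.1%, which matches the stated 77%. Without the correction it is 83.3%.

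The 77% therefore belongs to a post-treatment comparison of AS1+SP with one other arm.

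**3. The same question asked through pre/post changes**

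Inputs from section 13.3: 50→90% and 50→70%. Assumptions: 67 post samples per arm, and pre and post samples treated as independent.

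- 67 pre samples per arm: SE = √[(2·0.25 + 0.09 + 0.21)/67] = 0.109. z = 0.20/0.109 − 1.96 = −0.13, so power is about 45%.
- 111 pre samples per arm (assumption: 336 × 0.33, the June 1995 parasite rate in section 1.3): SE = √(0.50/111 + 0.30/67) = 0.095, so power is about 56%.
- Same approximation without baselines: SE = √(0.30/67) = 0.067, so power is about 85%.

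The like-for-like drop is from 85% to between 45% and 56%.

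**4. A limit on the 77%**

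The 67 are expected clinical cases, whereas section VI.8 genotypes slide-positive children at the surveys. Having 67 requires 20% slide positivity among 336 children. At the 11% seen in treated children at the end of the 2002 season, 336 × 0.11 = 37 per arm, and the same corrected formula gives 46%.

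**5. Denominators**

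Inputs from section IV.2.3 (2002 trial): parasite prevalence 11% on sIPT and 35% on placebo; triple mutants 95% and 75% of parasites. Assumption: these shares apply per infected child.

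- Among infected children: 95% vs 75%, a difference of +20 points.
- Among all children: 0.11 × 0.95 = 10.5% vs 0.35 × 0.75 = 26.3%, a difference of −15.8 points and a ratio of 0.40.

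For two active arms at the planned 90% (AS1+SP) and 70% (other), per-child carriage reverses the order only if prevalence(other) × 0.70 > prevalence(AS1+SP) × 0.90. That needs a prevalence ratio above 0.90/0.70 = 1.29. With AS1+SP at 11%, the other arm would have to exceed 14.1%.

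**The case against.** **The AS1+SP contrast is in the protocol.** A reader of section VI.8 alone might infer that the trial never tests selection against AS1+SP. The document as a whole does not support that. Section 4 powers the contrast, and section 13.3 names AS1+SP as comparator and tabulates by regimen. A statistical analysis plan could also fix the test. This stands, and it makes the defect a conflict between sections rather than a missing comparison. The conflict remains, because section VI.8 is the place that states how *dhfr* and *dhps* will be compared.

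**AS+AQ is a reasoned control.** It is the only arm without an antifolate in a trial without placebo, it is randomised, and it is sampled at the same two surveys. A reader might infer that pre/post change confounds drug selection with season, since about 50% at baseline and 75% in placebo children suggest a 25-point rise without drug. The documents do not support this. The concurrent control can absorb a shared seasonal change. The 50% comes from section 13.3 and the 75% from section IV.2.3, and they may not describe the same marker: the corresponding treated end values are 90% and 95%. Section IV.2.3 also reports that selection was not seen in the control group.

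**Infected-only prevalence is the endpoint as worded.** A reader might infer that restricting to slide-positive children makes the analysis wrong in sign. It does not. For an endpoint defined among parasites, 95% against 75% is the correct direction, and section IV.2.3 already gives the other side: "Although there was no overall increase in the number of resistant parasites in the children who had received sIPT". Per-child carriage answers a different question. The reversal is shown for sIPT against placebo, not between active arms, and it owes nothing to the pre/post design or to the choice of control.

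**Conclusion.** The point holds as an internal inconsistency. Section VI.8 states a *dhfr*/*dhps* analysis that neither separates AS1+SP from AS3+SP nor uses AS1+SP as reference, so it does not match sections V, 4 and 13.3 and, followed literally, does not test the resistance hypothesis. The choice also affects power: 77% as stated applies to the between-arm December comparison, and a difference of pre/post changes would have about 45% to 56%. Those last figures rest on independent pre and post samples, 67 post samples per arm and an assumed 67 to 111 baseline samples.

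The denominator is a reporting matter rather than an error. The 2002 figures show that the two measures can disagree in direction. Between active arms at the planned 90% and 70%, disagreement needs a parasite prevalence ratio above about 1.29. The documents give no December 2004 prevalence by arm, so whether that will occur is unknown.

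**What to change.** Reconcile sections V, 4, VI.8 and 13.3 as follows.

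1. Name as the main *dhfr*/*dhps* analysis the December between-arm comparison of AS3+SP, AS+AQ and Lapdap, each against AS1+SP. Use the *dhfr* 108/59/51 definition on which section 4 is powered.
2. Keep the pre/post change with AS+AQ as control, by separate arm, as a supporting analysis. Keep the swapped-role *pfcrt* comparison likewise, since AS1+SP as a single reference does not by itself settle how amodiaquine selection is judged.
3. Report two measures side by side: prevalence among slide-positive isolates (the endpoint as worded), and carriage of the resistant genotype among all children surveyed, with slide-negative children counted as non-carriers.
4. Restate the power for the number of slide-positive children expected in December.

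The cost is wording and one further table. Parasites are already to be measured in every child at both surveys (section 7), and filter papers are already to be collected there (section VI.8). The downside is small: per-child carriage mixes infection with selection and misses infections below slide detection, so it should not be shown without the isolate-level figure.

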Parents and legal guardians will also be informed that, on medical grounds, the principal investigator may decide to withdraw the patient. Reason(s) for this withdraw will be noted in the patient record form. In this case as well, study subjects will keep on receiving all the advantages enjoyed by continuing participants.

11. Monitoring

Clinical monitoring will be done as decided by the Consortium. Basically, a Data and Safety Monitoring Board (DSMB) will be set up with the agreement of the London School of Hygiene and Tropical Medicine (LSHTM), the Dakar University (UCAD) and the National Malaria Control Programme (PNLP). Reports of all cases of death will be given to the DSMB.

The DSMB will review the trial protocol and Standard Operating Procedures (SOPs) before the trial commences and decide on the reporting procedure that it requires.

All serious adverse events that occur within seven days of drug administration will be reported to the DSMB.

12. Recruitment and training of staff

Before commencement of the study, three nurses, two field supervisors, two drivers, seven field workers, two-biologist technicians and two data entry clerks will be recruited. A logistician and an IT manager are also needed for the study. Additional staff may be engaged when needed.

A two-day workshop will be held in early August 2004. During this meeting, the principal investigator will explain the aim of the study. Tasks will be allocated with detailed explanations of expectations for each member of the group. A formal assessment of the impact of the workshop on the participant’s understanding of the study procedures will be held. Last but not least, a strong team spirit will be built up during this retreat.

Finally a one-week pilot study will be organised including organisation of drug distribution in the field.

13. Data management

The first step of the data processing will deal with the selection of the approximately 1680 children aged from 1 to 6 years needed for the study (20% future refusal or loss to follow-up taken into account). This will be done using the demographic database of Niakhar.

13.1. Design and organisation of the trial database.

Information will be collected from two sources:

►From the Niakhar demographic database

Identification information of each individual: identification number, surname, first name, date of birth, gender, residency, and identification of parent

►From the sIPT trial

Drug administration: date and place of event

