# 15. Ethical considerations

The conclusions of this study could influence malaria control policies in Senegal and in other parts of Africa. Parents and guardians will profit from the intensive surveillance activities during the study period. In addition, all malaria cases will be treated in health centres according to national policy. Thus, this study will not interfere or limit access of study participants to the national malaria prevention programme provided by the health services.

Three of the drug combinations to be used in the study, SP + one dose of artesunate, SP + three doses of artesunate and amodiaquine + artesunate have been used extensively to treat or prevent malaria in young children in Africa and their safety profiles are well known. There is less safety data for Lapdap but this drug is now licensed for the treatment of malaria in Europe and in many countries in Africa.

Informed and written consent will be obtained from parents or guardians. The study will explain the need to find an alternative to SP for seasonal IPT since this is important for future protection of their children.

Ethical approvals of the study will be sough from both:

- the Ethics review board of Research for Development Institute in France,
- the Senegalese Ethics Committee
- and the Ethics committee of the London School of Hygiene and Tropical Medicine.

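### Non-fatal hospital admissions more than seven days after a dosing round are not classed as adverse events and do not routinely reach the DSMB, although comparing safety is a specific objective

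*Protocol*

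**What the plan says.** Section VI.9 (Assessments of adverse events) sets the definition: "Adverse events will be defined as any signs or symptoms, which first develop or increase in severity within seven days after intake". The next sentence sets the rule for serious events: "Any serious adverse events such as death or admission to hospital which occur within one week of drug administration" are to be investigated and reported to the DSMB within 24 hours. Hospital admission is therefore named as a serious event, but the duty to investigate and report it ends after a week.

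Section VI.11 (Monitoring) repeats the limit: "All serious adverse events that occur within seven days of drug administration will be reported to the DSMB". It makes one exception, with no time limit: "Reports of all cases of death will be given to the DSMB". It also lets the DSMB settle, before the trial starts, what reporting procedure it wants.

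The drugs are "given three times in early September, early October and early November 2004" (Study design). Section III makes the comparison of safety across the four regimens part of the specific objective. Section VI.15 (Ethical considerations) concedes: "There is less safety data for Lapdap".

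Two other places bear on the safety summary. The monthly list in section VI.13.3 includes a proportion of serious adverse events after dosing, and section VI.14 bases safety on information gathered after each round. Neither states a window, and neither gives another definition of an adverse event.

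**The concern.** Rounds are a month apart and the definition closes after a week. A child admitted alive on day 8 or later has, on the protocol's own wording, no adverse event. The admission is not investigated as one and does not enter the routine flow to the DSMB. An analyst who follows the definition would leave it out of the safety comparison.

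Two kinds of information are at stake. One is the delayed serious reaction that appears after the first week. The other is a difference between arms in later admissions, whatever the cause, which needs no attribution to the drug to be informative in a randomised comparison. These drugs are given to children whether or not they have parasites or symptoms, and one regimen is acknowledged to have less safety data, so both kinds matter to the stated objective.

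**Working it through.** The protocol gives no figure for the time its safety windows cover, so there is none to reproduce. The check is person-time arithmetic followed by a reading of the text.

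**Inputs**
- Rounds: three, at the start of September, October and November (Study design). I take the first of each month.
- Window: seven days per round (sections VI.9 and VI.11).
- Follow-up: September to December in section VI.7, which is 30 + 31 + 30 + 31 = 122 days. Section VI.17 gives five months from 1 September, which is 122 + 31 = 153 days.
- Dosing days per round: one day of artesunate in one arm, three days of drug in the others, for example "Artesunate plus Amodiaquine both given for three days".

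**Share of time covered** = (rounds × window) / (days from first dose to end of follow-up)
- Four months: 3 × 7 / 122 = 21 / 122 = 17.2% inside, 101 days (82.8%) outside.
- Five months: 21 / 153 = 13.7% inside, 132 days (86.3%) outside.

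**Where the uncovered days lie (four months)**
- September round: 30 − 7 = 23.
- October round: 31 − 7 = 24.
- November round to 31 December: 61 − 7 = 54.
- Total: 23 + 24 + 54 = 101. More than half follow the last round.

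**Sensitivity**
- If the seven days run from the last of three daily doses, each round covers about 9 days: 27 / 122 = 22.1% inside and 77.9% outside, or 27 / 153 = 17.6% inside and 82.4% outside.
- If the first round is on 5 or 10 September and follow-up ends on 31 December: 21 / 118 leaves 82.2% outside, and 21 / 113 leaves 81.4% outside.
- If follow-up is cut at an early December survey (91 days): 21 / 91 leaves 76.9% outside.

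On either follow-up period the protocol states, between 78% and 86% of the time lies outside the windows.

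**Illustration in events.** The protocol gives no admission rate. Assume 2% of children are admitted over four months (range 1% to 5%). With 420 per arm that is 420 × 0.02 = 8.4 admissions (4.2 to 21.0). At a constant rate, 8.4 × 21 / 122 = 1.4 (0.7 to 3.6) fall inside the windows. The constant rate is itself an assumption. Drug reactions that cluster after dosing would place more inside.

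**Does any other section capture later admissions as safety events?** The trial data listed in section VI.13.1 are drug administration, morbidity (date and symptoms), blood sampling and anthropometry. Admission is not among them. The health-centre form in Appendix 4 has columns for diagnosis, treatment and comment but none for admission or outcome. Appendix 3 is not available to me, so I draw nothing from it.

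**The case against.** The strongest reply is that Monitoring sets a reporting rule, not a counting rule. The sections on summary and analysis (VI.13.3 and VI.14) contain no window, and detailed tabulation may sit in an analysis plan that is not shown. This stands as far as the Monitoring sentence alone is concerned. It does not remove the point, because the seven-day limit is in the definition of an adverse event in VI.9 and no other section replaces it.

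A reader might infer several stronger things that the protocol does not support:

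- **That about four-fifths of the safety information is lost.** The arithmetic gives a share of calendar time. Acute reactions are likely to come soon after dosing, so the windows may hold far more than 17% of the drug-related events.
- **That later illness goes unseen.** Section VI.7 provides weekly home visits and free consultations, and VI.13.2 brings both active and passive surveillance into the data. The gap is in how admissions are classified and where they are sent.
- **That the DSMB cannot learn of later admissions.** It may set its own reporting procedure. Nothing in the text, however, sends them by default.
- **That the three-day regimens are watched for less time after the last dose.** This holds only if the seven days run from the first dose of a round. The text speaks of intake and of drug administration and does not fix the starting dose. About two days are at stake.
- **That deaths are too few to matter and admissions carry most of the evidence.** Section VI.1.3 reports malaria mortality of 16 per thousand per year, said to be one in four deaths in children aged one to four. Taken at face value, 16 × 4 = 64 per thousand per year, and 420 × 0.064 × 122 / 365 is about 9 deaths per arm before any protection. Deaths may be informative, but they do not stand in for non-fatal admissions.

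It is also true that many later admissions in the transmission season would be malaria, and that the comparison would be weak. At the assumed 2%, 420 per arm gives 80% power (two-sided 5%) only for a rise to about 5.7%. That limits what the extra data could show. It is not a reason to discard them.

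**Conclusion.** The point holds in a limited form. Followed as written, the protocol leaves non-fatal admissions from day 8 after a round outside the definition of an adverse event and outside routine DSMB reporting. The windows cover 17% of the four-month follow-up or 14% of the five-month one, and about 18% to 22% if each window is stretched to nine days. These shares rest on rounds at the start of each month and describe time only. How many drug-related events fall outside cannot be derived from the document.

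The consequence is an incomplete safety comparison, chiefly for delayed serious reactions and for later differences in admissions between arms. It is not an unmonitored trial: deaths are reported without limit, later illness is recorded, and the board can ask for more. The change is worth making. The four-month and five-month follow-up statements should also be reconciled, though either one supports the conclusion.

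**What to change.** In sections VI.9 and VI.11:
- Record every hospital admission from first dose to end of follow-up, with no time limit, as is already done for deaths. Use the existing weekly visits and health-centre contacts, and add a field for admission and its outcome to the Appendix 4 form.
- Include these admissions in the periodic reports to the DSMB.
- Tabulate them by arm, by days since last dose and by diagnosis. Counting from the last dose also removes the uncertainty about which dose starts the clock.
- Leave the 24-hour reporting for the seven-day window as it stands.

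The cost is a few more forms and one more table. The drawback is that malaria admissions will be included. The split by diagnosis separates them, and the split by days since dose keeps the early post-dose period visible.
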